**Methods::**

The study is a 6-month, randomized controlled parallel-group, single-blinded clinical trial. Institutionalized patients with Alzheimer disease will be included. The intervention group will perform a multicomponent physical exercise program in reduced groups, with a frequency of 3 sessions per week, associated with a Mediterranean diet. This program includes strength, balance, and aerobic resistance exercises, and in the main part of the session, also ludic exercises to improve agility, coordination, and balance. The control group will receive usual care. The outcomes to assess are the change of physical functions, such as gait and balance, and the change of bone mineral density by calcaneal quantitative ultrasound, during the study follow-up at 1, 3, and 6 months. This clinical trial will generate more and new evidence on the effects of a multicomponent physical exercise program and Mediterranean diet in patients with Alzheimer disease on risk of falls and osteoporotic fractures, the relation of these with bone mineral density, gait and balance, and the correlations between them.

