POMA-T: We will perform the original POMA-T 28-point version. It consists of a balance scale [Balance performance oriented mobility assessment (POMA-B)] and a gait scale [Gait performance oriented mobility assessment (POMA-G)]. POMA-B can score 16 points (sitting balance, get up and sit up from a chair, immediate standing balance in the first 3 to 5 seconds, standing balance, balance with eyes closed and turning balance 360°). POMA-G can score 12 points (initiation of gait, step height, step length, step symmetry, step continuity, path deviation, trunk stability, and walk stance). Less than 19 points means high risk of falls, between 19 and 24 means risk of falls, and between 24 and 28 means no disturbance in gait or balance. Therefore, the POMA-T's cutoff point that predicts moderate or high risk of falling and disturbance in balance and gait was 24.^[16,17,22,82,83]^TUG: Is an easy tool to evaluate the gait and balance. It measures the time in seconds for the subjects to get up from a standard armchair, walk 3 m, turn, walk back to the chair and sit down. The cut-off point for normal mobility is 12 seconds and values > 30 seconds indicate a high level of dependence,^[30,84,85]^ although other authors are somewhat stricter with the interpretation of the TUG, in such a way that with a time <10 seconds, it is considered normal; <20 seconds mobility difficulties and low or moderate risk of falls; > 20 mobility problems with need of help and high risk of falls.^[84]^Calcaneal QUS: The bone health status will be assessed by ultrasound bone densitometry/sonometry. It is a safe, radiation-free modality that provides precise quantitative assessment of skeletal status, useful information in elderly for identifying patients at risk of developing osteoporosis and for assessing their risk of future fracture.^[79,80,86]^ Bone mass we will measured at the calcaneus (95% of trabecular bone) by using QUS (Sahara Hologic Clinical Bone Sonometer; Hologic lnc., Waltham, MA). QUS parameters will be measured, but we consider the estimated BMD (g/cm^2^) and T-score (comparison of the average mineral density of the patient's bone with a healthy young people) as primary outcome, because some researchers suggested that these parameters are more useful in the determination of subjects with low bone health status.^[79–81,86]^

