### Statistical analysis

2.9

Data will be analyzed by using the IBM-SPSS software package (version 23.0). Descriptive data analysis will be reported by groups as means ± standard deviation for quantitative variables and as frequencies and percentages for qualitative variables. In the graphical representation, bar graphs by groups will be used for quantitative variables, and pie charts to represent categorical variables. The main change from baseline to 6 months will be calculated by using intention-to-treat analysis for each outcome measure.

Initially, for comparisons between groups at baseline, *t* tests or Mann–Whitney *U* tests will be used for continuous variables, depending on normality, which will be checked for each using the Kolmogorov–Smirnov test and normal probability box-plots, and the Chi-square test or Fisher test will be used for quantitative variables.

To analyze the efficacy of the multidomain intervention on the outcome variables, both in the primary and secondary outcomes, multivariate analysis of variance (MANOVA) will be applied with repeated measures (4 levels) to assess interactions between the factors and differences by categorical variables, with covariates, and pairwise comparisons post-hoc to determine whether there are significant differences between groups and within groups. The effect size for the MANOVA model will be calculated by the partial eta square (η^2^) that shows how much variance is explained by the independent variable.

We will carry out correlations with Pearson *r* coefficient to determine whether the values of 2 or more quantitative variables change in conjunction or are related in some of the moment of the study (time-factor in the statistical model).

For the analysis of the falls data, we will calculate the incidence rate during the study and the prevalence proportion by group and by sex at the end of the study (point prevalence). Subsequently, we will calculate the relative risk to estimate the magnitude of the association between the participation to the MPEP and falls, and indicate the likelihood of fall in the intervention group relative to the control group and also by sex.^[91]^

The statistical analysis will be conducted at a 95% confidence level. A *P* value < .05 will be considered to indicate statistical significance in all analyses.

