## Discussion

3

This study is part of a line of research and has been planned in the context of physical exercise as a nonpharmacological treatment, along with other interventions such as diet, in elderly and patients with cognitive impairment, considering them as vulnerable or frail population. There are many studies that are showing the beneficial effects of physical exercise on the changes of aging in elderly^[52,54,57,70]^ and in patients with cognitive decline.^[3,24,30,31,35,36,40,56,58]^ Patients with AD are a growing population group, with disturbing epidemiological data for a near future with important consequences from the health, social, and economic points of view.^[4,5]^

For these reasons, in this study, we want to evaluate the short and medium-term effects of a MPEP associated with a MeDi in people with AD on aspects that can improve their quality of life and their degree of autonomy. Taking into account the frailty of this population and the comorbidities correlated to cognitive decline and aging, we will evaluate a large number of outcome variables to assess the impact of the proposed intervention program on physical functions and bone health status with the intention of reducing the risk of falls and its serious consequences, mainly fractures. In such a way, that this MPEP with a MeDi has several specific objectives that attempt to avoid, delay, and/or minimize some of the frail conditions of these patients.

In our study, we want to contribute to the evidence on the reduction of bone fractures and their consequences. To do this, we plan to reduce the risk of fractures, intervening to decrease bone mass loss and the risk of falls as the main causal factors of fractures in older people and, even more, in people with cognitive impairment, such as patients with AD. There are studies that have addressed these aspects separately, but there are no studies that have worked on them together, and we will also look for associations or correlations between them. For this reason, we also will create a registry of falls to see the preventive effect of the intervention, as well as the relationships of each outcome variable with falls. During the 6 months of the study, changes in BMD, gait and balance, and nutritional status will be monitored and analyzed.

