### Strengths and limitations

3.1

We consider having some strengths points in our study. The design of this study has been based on the experience and results of previous pilot study and preliminary nonrandomized controlled clinical trial. The procedures will be carefully conducted by a multidisciplinary professional group highly qualified in the care and treatment of patients with AD. The novelty of our study is based on the fact that it is the first longitudinal clinical trial aimed at assessing the effects of a MPEP with a MeDi in short- and medium-term over 6 months on the bone health status and the risk of falls by correlating them with gait and balance disorders.

Some limitations of this study should be noted. General conclusions can only be drawn with caution and no conclusions about our intervention results should be drawn beyond institutionalized patients with AD, which suggests that they are more affected. Finding eligible elderly people with AD, who do not attend a center where they receive some type of intervention with physical exercise, is currently difficult, which makes intervention biases easily can appear. This can considerably increase drop-out rate during follow-up and the length of the recruitment period. Other studies should attempt to address strategies to increase the recruitment capacity of eligible patients for the control group, and to carry out experimental designs with 2 or more intervention arms.

In our future studies, in the same line of research, we also want to assess in greater depth the impact of diet combined with exercise on our outcome variables and analyze the influence of the nutritional status of patients with cognitive impairment, as well as their relationships with physical, cognitive, and bone health. And the study results will be released to the participating physicians, referring physicians, patients, and the general medical community.

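### Section 2.9 opens an unrestricted set of correlations to a P < .05 significance rule without calling them exploratory; bone by gait and balance alone allows 140 tests

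*Protocol article*

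**What the plan says.** Section 2.9 (Statistical analysis) plans Pearson coefficients to determine whether "values of 2 or more quantitative variables change in conjunction or are related in some of the moment of the study". This covers both joint change and association at a given time. It names no pair of variables, no visit and no change interval. The section ends with the rule that a P "value < .05 will be considered to indicate statistical significance in all analyses". It does not set the correlations apart from that rule or call them exploratory.

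Other sections give these correlations some weight:

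- The Methods paragraph of the abstract lists, among the evidence the trial will generate, "the relation of these with bone mineral density, gait and balance, and the correlations between them".
- Section 3.1 (Strengths and limitations) describes the novelty as a first longitudinal trial of the programme's effects "on the bone health status and the risk of falls by correlating them with gait and balance disorders".
- Section 3 (Discussion) says "we will also look for associations or correlations between them" and announces a falls registry to study the preventive effect "as well as the relationships of each outcome variable with falls".

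The outcome measures themselves are ranked. Section 2.7.1 makes POMA-T and TUG primary and, for the ultrasound, says "we consider the estimated BMD (g/cm^2^) and T-score" are primary. Section 2.7.2 makes OLB, FR, BUA, SOS and QUI secondary. Section 2.9 does not carry this ranking over to the correlations.

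**The concern.** The two sentences in section 2.9 work together. The first lets any pair of quantitative variables be correlated, at any visit or as a change. The second lets each of those tests be called significant at 0.05. With that many looks, some nominally significant coefficients are to be expected when bone status and physical function are unrelated, and nothing in the text says which coefficient answers the question.

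What is at stake is how the bone-function results are read. A reader of the final report could be shown a few significant correlations in support of a link that the abstract and section 3.1 advertise, with no means of telling them from chance findings. The problem remains whichever correlation coefficient is used, and it is separate from the tests of the primary outcomes.

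This is more than a detail left to an analysis plan. Restricting or adjusting the correlations there would conflict with a rule that the article states for all analyses.

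**Working it through.** **The plan's own figure.** The article gives no count or error rate for the correlations, so the only figure to reproduce is the sample size (section 2.8: difference 1.5, SD 2, two-sided alpha 0.05, power 80%, drop-out 33%).

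- Per arm: 2 x (1.96 + 0.8416)^2 x 2^2 / 1.5^2 = 27.9, rounded up to 28.
- With drop-out: 28 / 0.67 = 41.8, rounded up to 42 per arm, 84 in total. This matches.
- The check below therefore uses N = 84 (all randomized) and N = 56 (2 x 28 completers).

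**Counting the tests.**

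- Bone measures: estimated BMD, T-score, BUA, SOS, QUI = 5 (sections 2.7.1 and 2.7.2).
- Gait and balance tests: POMA-T, TUG, OLB, FR = 4 (same sections).
- Times: baseline, 1, 3 and 6 months = 4 visits, hence 3 changes from baseline (section 2.7).
- Same-visit correlations: 5 x 4 x 4 = 80.
- Change-from-baseline correlations: 5 x 4 x 3 = 60.
- Total: 80 + 60 = 140.
- Primary measures only, same visit: 2 x 2 x 4 = 16.

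The POMA subscales, MNA and falls would add more. They are left out here.

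**Expected false positives with no true link.** The number of tests times 0.05, whatever the dependence between tests: 80 x 0.05 = 4; 140 x 0.05 = 7; 16 x 0.05 = 0.8.

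**Chance of at least one.** If the tests were independent it would be 1 - 0.95^80 = 98.3%, 1 - 0.95^140 = 99.9% and 1 - 0.95^16 = 56%. They are not independent: QUI is computed from BUA and SOS (section 2.7.2), the T-score re-expresses the bone measurement, and visits repeat the same measures in the same patients. The figures below come from simulation with zero correlation between bone and function. All correlations within each domain and across visits are assumptions, because the article gives none. N = 56 and N = 84 give nearly the same results.

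| Assumed correlation: bone / function / across visits | 80 tests | 140 tests |
|---|---|---|
| 0.5 / 0.5 / 0.5 | 92% | 99% |
| 0.7 / 0.5 / 0.7 | about 83% | 96% |
| 0.8 / 0.5 / 0.8 | 72% | about 93% |
| 0.9 / 0.6 / 0.8 | about 60% | 84% |
| 0.95 / 0.7 / 0.9 | 41% | about 70% |
| 0.99 / 0.8 / 0.95 | about 25% | about 52% |

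A second structure makes QUI the sum of BUA and SOS and the T-score a linear function of BMD. It gives about 37% to 74% for the 80 and 70% to 92% for the 140.

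For the 16 primary-measure tests, the settings tried gave 35% (0.9 / 0.5 / 0.7), 30% (0.95 / 0.5 / 0.8) and 23% (0.95 / 0.7 / 0.9). These settings do not span the extremes in the table, so that range would widen in both directions under them.

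**After a fix.** Two pre-named correlations, unadjusted and independent, carry 1 - 0.95^2 = 9.75%. Holm adjustment brings this to at most 5%. Correlations reported without significance claims need no threshold.

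**The case against.** The strongest reply has three parts.

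*A condensed article need not list pairs and visits.* That is so, and the absence of a list alone would be no finding. What stands is that the article states a significance rule for every analysis and applies it to an open set of correlations.

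*The correlations are secondary in the design.* They are not among the primary or secondary outcomes, the sample size rests on POMA-T alone, and efficacy is tested by repeated-measures MANOVA. All of this is correct. A reader might infer that the correlations are the trial's novelty, or that any one significant pair would be taken to confirm a bone-function link. The article supports neither. The novelty sentence in section 3.1 is about assessing the effects of exercise with diet, and the correlations are one clause of it. No decision rule tied to a single coefficient is stated.

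*The bone measures are largely redundant, so the tests are far fewer than they look.* This is right about the chance of at least one false positive, which falls to about 25% for the 80 tests under extreme redundancy. A statement that a chance finding is more likely than not therefore cannot be made for the same-visit tests without assuming particular correlations. For the 140 tests, the probability stayed just above one half even in the most extreme setting. Redundancy leaves the expected number of false positives unchanged; it makes them come in clusters, which can look like corroboration.

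**Conclusion.** The point holds as one about interpretation. Section 2.9 attaches P < .05 to an open set of correlations to which the abstract and section 3.1 give a role in the trial's evidence and novelty.

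- **Firm:** the counts (80 same-visit, 140 with changes) and the expected false positives with no true link (4 and 7). They rest only on the listed measures, the visits and the stated threshold. Neither 80 nor 140 is a ceiling.
- **Dependent on assumed correlations:** the chance of at least one false positive, roughly 25% to 92% for the 80, 50% to 99% for the 140, and about a quarter to just over a third for the 16 primary-measure tests in the settings tried. The lowest of these is still more than four times the nominal 5%.

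It would be wrong to infer a flaw in the trial's main result: the randomized comparison and the sample size of 84 are untouched. The text should be changed, but the trial does not depend on it.

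**What to change.** Add to section 2.9 that the correlations are exploratory, are reported as r with a 95% confidence interval and without significance claims, and are exempt from the sentence applying P < .05 to all analyses. This is the core of the remedy and takes a few lines.

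If the sponsor wants a confirmatory statement about bone and function, it should be named in advance from the measures already ranked primary. One reasonable choice is the 6-month change in estimated BMD with the 6-month change in POMA-T and in TUG: two tests, Holm-adjusted (smaller P against 0.025, then the other against 0.05). The 6-month interval is the one section 2.9 already uses for its main change. Other pre-named pairs would serve equally well.

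No new data or patients are needed. The cost is that all other correlations become hypothesis-generating only, and the wording on correlations in the abstract and section 3.1 should be read, and reported, in that light.

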#### Primary outcome variables

2.7.1

The primary outcome measures are the change in gait, balance, and bone health status during the study follow-up.

Physical functions such as gait and balance will be assessed by the POMA-T and the TUG. Both of them are widely and easily used tools applied in clinical settings with older adults and AD patients.^[16,30]^ And bone health status will be assessed by quantitative ultrasound (QUS).^[79–81]^

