### Sample size calculation

2.8

The sample size calculation has been made based on the potential modification of the score of the POMA-T. For this, we have considered the results obtained in the previous pilot study with 9 patients in a 1-month follow-up, and the preliminary trial with 72 participants with a ratio of 3:1 to the intervention group and the control one during 6 months. In the pilot study, the POMA-T was modified by 1.7 points. Then, in the preliminary trial, we accepted to calculate the sample size, as statistically significant, with a difference greater than or equal to 1.7 points with a dropTout rate of 15%.

In our current study, the sample size has been estimated to conduct a randomized controlled clinical trial with a 1:1 ratio between the 2 groups. In this new calculation, considering the data from the pilot study and some of the available data from the preliminary trial, we have reduced the minimal detectable change in the POMA-T to 1.5 points, with a standard deviation of 2 points and we have increased the drop-out estimated rate during the study to 33% by the difficulty to avoid intervention biases in the control group fundamentally. Therefore, with this, and accepting an alpha risk of 0.05 and a beta risk of 0.2 in a 2-sided test, 84 subjects are necessary, 42 in each group. The sample size calculation was made with the software “GRANMO sample size and power calculator” (7.12 version).

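### Four unranked primary measures are each judged at P < .05 with no success rule, while only POMA-T was sized: family-wise error is about 12-16% if any one counts as success

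*Protocol article*

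**What the plan says.** - **Primary outcomes (section 2.7.1).** The section opens: "The primary outcome measures are the change in gait, balance, and bone health status during the study follow-up". POMA-T and TUG measure gait and balance, and calcaneal ultrasound measures bone health. Within ultrasound, two parameters are singled out: estimated BMD, and the T-score, which compares the patient's bone density "with a healthy young people) as primary outcome". That makes four primary measures. No order among them is given, and no rule for what counts as a positive trial.
- **Sample size (section 2.8).** "The sample size calculation has been made based on the potential modification of the score of the POMA-T". The inputs are a 1.5-point difference and an SD of 2, "accepting an alpha risk of 0.05 and a beta risk of 0.2 in a 2-sided test", with 33% drop-out. The result is 84 participants, 42 per group. No power is given for TUG, BMD or T-score.
- **Analysis (section 2.9).** A repeated-measures MANOVA with four levels is applied to primary and secondary outcomes, followed by "pairwise comparisons post-hoc to determine whether there are significant differences between groups and within groups". One sentence points to the change from baseline to 6 months, by intention to treat, for each outcome. The section closes with the rule that a P "value < .05 will be considered to indicate statistical significance in all analyses".

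**The concern.** The three sections do not fit together. Section 2.8 treats the trial as having one test at 5%. Section 2.7.1 gives it four primary measures, and section 2.9 gives each of them the full 5%. With no success rule, one significant result out of four could be reported as a positive primary finding, so the chance of a false claim exceeds the 5% that the reader will assume. If the analysis is corrected later, the power stated in section 2.8 no longer applies.

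Two further features add to this. By the protocol's own definition the T-score re-expresses the same density as estimated BMD, so it adds a primary label with little separate evidence. Significance within a group is also listed beside significance between groups, although a within-group change does not test the effect of the intervention.

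**Working it through.** **1. Reproduce the stated sample size.** Inputs from section 2.8: difference 1.5 ("we have reduced the minimal detectable change in the POMA-T to 1.5 points"), SD 2 ("with a standard deviation of 2 points"), two-sided alpha 0.05, power 0.80, drop-out 33%.

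- n per group = 2 × [2 × (1.960 + 0.842) / 1.5]² = 27.9, so 28 evaluable.
- 28 / (1 − 0.33) = 41.8, so 42 randomised per group and 84 in total. This matches the plan.

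The plan's 80% power therefore belongs to a single POMA-T test at 0.05 with 28 completers per arm.

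**2. Family-wise error, one test per primary measure, each at 0.05.**

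- Four independent tests: 1 − 0.95⁴ = 18.5%.
- Three independent tests (T-score an exact duplicate of BMD): 1 − 0.95³ = 14.3%.

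The measures will not be independent, and the document gives no correlations. The following are assumptions: BMD with T-score 0.9 to 1.0; POMA-T with TUG 0 to 0.8 in absolute value; physical with bone measures 0 to 0.2. Simulation of correlated two-sided z-tests (1,000,000 draws) gives:

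| POMA-T/TUG | BMD/T-score | Physical/bone | Family-wise error |
|---|---|---|---|
| 0 | 0.9 | 0 | 16.1% |
| 0.5 | 0.99 | 0.2 | 14.0% |
| 0.8 | 1.0 | 0.2 | 12.3% |

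The range is about 12-16%. No post-hoc or visit-specific tests are counted in it.

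**3. POMA-T power if the primaries were Bonferroni-corrected.** Standardised difference d = 1.5 / 2 = 0.75; noncentrality = d × √(n/2), which is 2.81 for n = 28 and 3.44 for n = 42.

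| Evaluable per arm | Alpha | Noncentral t | Normal approximation |
|---|---|---|---|
| 28 | 0.05 | 78.7% | 80.1% |
| 28 | 0.05/3 | 63.2% | 66.0% |
| 28 | 0.05/4 | 59.0% | 62.1% |
| 42 | 0.05/4 | 80.9% | 82.6% |

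**4. Sample size to keep 80% power under Bonferroni (normal approximation, 33% drop-out).**

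- Three tests: 38 evaluable; 38 / 0.67 = 56.7, so 57 per group, 114 in total.
- Four tests: 40 evaluable; 40 / 0.67 = 59.7, so 60 per group, 120 in total.

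A fixed sequence that starts with POMA-T tests it at the full 0.05, so 84 stands.

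**The case against.** **Multiplicity may be left to an analysis plan that is not shown.** This stands in part for the post-hoc comparisons: adjusted P values judged at .05 would not contradict section 2.9, and the method of adjustment is ordinary analysis-plan detail. It does not cover the primaries. The protocol itself names four, sizes one and states the threshold for all analyses.

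**Success might require all four measures.** Then no alpha correction would be needed. No such rule is stated, however, and power for the other three measures is not given.

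**Intention to treat could keep all 42 per arm.** Power for four Bonferroni tests would then be about 81-83%. That is a fair qualification, but section 2.8 plans for a 33% loss.

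**Stronger readings that the text does not support.**

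- A reader might multiply four measures by three follow-up visits and infer a family-wise error of 1 − 0.95¹² = 46%. That treats repeated measurements on the same patients as independent and counts T-score as separate from BMD. It also overlooks the sentence in section 2.9 that points to 6 months as the main change. Section 2.7.1 is looser about timing, which is an ambiguity and not three equal chances per measure.
- A reader might count every post-hoc pair and infer a number of expected false positives. Within-group changes can be real in a progressive disease even when the intervention does nothing, so they are not false positives about treatment. Baseline comparisons are not efficacy tests either.
- A reader might infer that BMD and T-score make the MANOVA near-singular. The four levels match the four assessments. The text does not say that the four measures enter one joint model. Nor does it describe an omnibus test that must be passed before the separate tests.

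**Conclusion.** The point holds in limited form. The protocol fixes four unranked primary measures, no success rule, an uncorrected threshold for every analysis, and a sample size for one measure only. If any one primary counts as success, the family-wise error is about 12-16% with one test per measure. This rests on the assumed correlations shown; 18.5% is the bound for independent tests. Even the lowest value is more than twice the nominal 5%. The stated 80% power is right for an uncorrected POMA-T test with 28 completers per arm and for nothing else in the primary set. This should be settled before any unblinded result is seen, because a choice of primary made afterwards could not be defended.

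**What to change.** In sections 2.7.1 and 2.9:

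- State that the confirmatory contrast is the between-group difference in change from baseline to 6 months.
- Test it in fixed sequence, each step at two-sided 0.05 and only if the previous step succeeded: POMA-T (matching section 2.8), then TUG, then estimated BMD.
- Report T-score descriptively.
- Report months 1 and 3, the secondary outcomes and within-group changes as estimates with 95% confidence intervals, and say that they are not evidence of efficacy.
- Limit the P < .05 rule to the confirmatory sequence.

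**Cost.** Wording in the protocol and analysis plan, and a registry update. There are no extra patients (N stays at 84) and no loss of POMA-T power. The real price is that bone health, which the study aim lists first, can be claimed only after POMA-T and TUG succeed.

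**Alternative.** If the sponsor wants bone health to keep equal primary status, Holm across POMA-T, TUG and estimated BMD also controls the error. The POMA-T power in section 2.8 must then be restated. With 28 completers per arm its guaranteed minimum is the three-test Bonferroni figure, about 63-66%.
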